### Image analysis

From each of the images the region of interest (ROI) will be manually selected from which the matrix of pixels from which the mean, standard deviation, variance, kurtosis and skewness, all first order parameters associated with the gray levels of each pixel, will be calculated.

The second-order parameters provide information on the spatial distribution of pixel gray levels from different methods:

Gray Level Co-Occurrence Matrices (GLCM), described by Haralick et al. [32, 33] which consist of comparing pairs of pixels separated by a certain distance (by default a value of 1 is used) and in an angular direction (0º, 45º, 90º and 135º) along the entire matrix, calculating the frequency with which certain gray levels appear in the image and their relationship between them. The parameters calculated are: homogeneity or second angular momentum, contrast, inverse difference, entropy, correlation, average sum, entropy sum, entropy difference, variance difference, variance sum, correlation measure A information, correlation measure B information, cluster shadow, cluster prominence, autocorrelation, dissimilarity, energy and maximum likelihood.

Gray-Level Run-Length Matrix (GLRLM) described by Galloway et al. [34] and calculated from the run-length statistic that represents a set of consecutive pixels having the same gray level in each of the four angular directions described along the whole matrix, obtaining the following parameters: gray level non-uniformity, high gray level run emphasis, long run emphasis, long run low gray level emphasis, run length non-uniformity, run percentage and short run emphasis.

Analysis of Local Binary Patterns (LBP) described by Ojala et al. [35] which consists of comparing the intensity of a central pixel, which is taken as a reference value, with those surrounding it, assigning them a value of 1 or 0 depending on whether their intensity is above or below the threshold value set by the central pixel, the resulting matrix is multiplied by the original, thus obtaining a matrix from which the final LBP parameter is calculated.

The blob analysis described by Nielsen et al. [36] is based on detecting areas close to each other with a similar eco-intensity called “blobs”. The number of blobs in each ROI is calculated as well as their average perimeter and standard deviation.

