### Statistical analysis

The R program version 4.3.1 will be used for statistical analysis. The level of significance will be set at *p* < 0.05. The distribution of quantitative variables, both baseline and outcome, will be tested with the Kolmogorov-Smirnov test with Lilliefors correction. Qualitative variables will be described in absolute values and frequencies and quantitative variables with mean and standard deviation.

Baseline and outcome variables differences using Barthel Index (BI) score dichotomized between dependent (BI < 60) and independent (BI > 60) patients [31] using *T*-test or U-Mann-Whitney for quantitative variables (depending on their distribution) and Fisher exact test for qualitative variables.

A multivariate analysis will be performed with a machine learning model through principal analysis using logistic regression, applying the model to 75% of the subjects and evaluating its accuracy in the remaining 25%, with the objective of creating a trained model that allows the development of therapeutic intervention plans that enable both the evaluation and treatment of patients. Model will be controlled by baseline variables with significant differences in univariate analysis.

Model will be constructed with dichotomized Barthel index as dependent variable and manual grip strength, EuroQoL-5D, NPRS, cross sectional area and thickness of the rectus femoris, STAI, TSK and BDI as explanatory variable. Logistic model will be selected instead of others used in machine learning (e.g. Random Forest, Support Vector Machines or Gradient Boosting) because it is computationally more efficient and faster and more easily interpretable.

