## DISCUSSION

The aim of this study is twofold: firstly, to investigate the correlation between muscle activation variables assessed via ultrasound and the comprehensive assessment of geriatric patients. This approach seeks to better understand how ultrasound findings may be related to the overall health and functional status of older patients. In addition, lastly published review found that ultrasound showed a low-to-moderate diagnostic test accuracy for sarcopenia, although included sample sizes was low (most studies less than 200 patients) and mostly only measured muscle thickness [41]. To counteract these limitations, this study has a large sample size with 500 patients and will measure muscle thickness but also cross-sectional area, as well as contraction potential and contraction-relaxation velocity with M-mode. Secondly, to analyze ultrasound images using histogram distribution to determine their correlation with mobi-mortality factors in frail patients. This approach will identify potential ultrasound markers that may be associated with a higher risk of complications in frail patients, as other studies found in the literature [42, 43].

To achieve these objectives, a study will be conducted on frail older adults, who will undergo a series of instrumental and functional tests designed to assess their functional capacity. Additionally, specific ultrasound images will be obtained to study sarcopenia and nutrition in this patient group. Subsequently, a comprehensive analysis of the correlation between all functional, ultrasound, and nutritional variables collected during the study will be conducted. This analysis will identify potential relationships between muscle activation, ultrasound image, and overall health and risk of complications in frail older patients.

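### Blob count per ROI and the two run-length non-uniformity parameters are confounded with ROI area unless ROI size is fixed or they are normalised

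*Protocol article*

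**What the plan says.** The Image analysis section of the protocol article starts from a hand-chosen region: "From each of the images the region of interest (ROI) will be manually selected". It gives no size, shape or pixel count for that region.

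The run-length parameters are "calculated from the run-length statistic that represents a set of consecutive pixels having the same gray level", taken in four directions over the whole pixel matrix. The list includes "gray level non-uniformity, high gray level run emphasis, long run emphasis" and ends with "run length non-uniformity, run percentage and short run emphasis". Neither non-uniformity parameter is described as normalised, and no formula is given. For the blob analysis the section states: "The number of blobs in each ROI is calculated as well as their average perimeter and standard deviation". The count is therefore specified per ROI, not per unit area.

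The Discussion gives the second aim as "to analyze ultrasound images using histogram distribution to determine their correlation with mobi-mortality factors in frail patients". The Samples subsection plans correlations between all functional, ultrasound, nutritional and psychological variables. The logistic model in the Statistical analysis section uses "manual grip strength, EuroQoL-5D, NPRS, cross sectional area and thickness of the rectus femoris, STAI, TSK and BDI as explanatory variable", so it already contains two size measures and none of the texture or blob parameters.

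**The concern.** A count per ROI depends on how much tissue the ROI covers. So do the two non-uniformity parameters in their usual form. Two patients with the same muscle texture but different ROI areas would then receive different values on all three.

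ROI area could differ between patients because the muscle is larger or smaller, or because readers draw differently. Muscle size is itself a study variable and may well differ between dependent and independent patients. A parameter that carries ROI area could then correlate with the Barthel Index, or with morbidity and mortality factors, through size alone, and be reported as an echotexture marker. The image-analysis aim is to find markers that add to thickness and cross-sectional area, so this would weaken its main result.

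**Working it through.** **The plan's own figure.** The article states no number for the blob or run-length parameters. Its one related figure, the sample size, reproduces: 100 + 50 × 8 explanatory variables = 500. Nothing below depends on it.

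**Inputs from the article.** The ROI is selected by hand with no fixed size; blobs are counted per ROI; gray level non-uniformity (GLN) and run length non-uniformity (RLN) are listed without normalisation.

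**Assumed inputs.** The standard definitions of GLN and RLN, the simulated texture, and the spread of ROI area. The article gives none of these.

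**Step 1: algebra.** Let p(g, r) be the number of runs with gray level g and length r, and N the total number of runs.

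- GLN = Σ_g [Σ_r p(g, r)]² / N
- RLN = Σ_r [Σ_g p(g, r)]² / N

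If the ROI is k times larger with the same texture, every p(g, r) and N rise by about k. Both parameters then rise by k² / k = k. The number of blobs also rises by about k, apart from edge effects. Dividing GLN and RLN once more by N, or blobs by area, removes the factor.

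**Step 2: simulation at fixed texture.** Smoothed Gaussian texture (scale 2 pixels), 16 gray levels, horizontal runs, blobs taken as connected areas more than 1 SD above the mean, 60 images per size:

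| ROI area (pixels) | Blobs | GLN | RLN | Run percentage |
|---|---|---|---|---|
| 3,600 | 21.4 | 232 | 1,064 | 0.611 |
| 14,400 | 77.2 | 919 | 4,187 | 0.608 |
| 57,600 | 293.6 | 3,661 | 16,711 | 0.607 |

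From smallest to largest, area rises 16-fold, blobs 13.8-fold, and GLN and RLN 15.7-fold each. Log-log slopes on area at texture scales 2 and 3 are 0.95 and 0.92 (blobs), 0.995 and 0.99 (GLN), and 0.99 and 0.99 (RLN). Short run emphasis, long run emphasis and run percentage, from the same list in the article, stay flat (slopes −0.006 to 0.014).

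**Step 3: 500 simulated patients in whom both texture and ROI area vary** (log-SD of texture scale 0.15). Each cell gives the correlation with ROI area, then with texture scale:

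| ROI-area CV | Blobs | GLN | RLN |
|---|---|---|---|
| 10% | 0.31 / −0.90 | 0.70 / −0.69 | 0.38 / −0.90 |
| 20% | 0.54 / −0.76 | 0.90 / −0.36 | 0.62 / −0.72 |
| 30% | 0.67 / −0.68 | 0.95 / −0.28 | 0.76 / −0.61 |
| 40% | 0.75 / −0.59 | 0.96 / −0.22 | 0.82 / −0.52 |

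With equal ROI areas (CV 0) the texture correlations are −0.93, −0.94 and −0.96.

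**Step 4: what this could do to a group comparison.** Assume 40 blobs on average, area CV 25%, Poisson counts given area, and a mean area d SD smaller in dependent patients. Blob density is identical in both groups.

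- Difference in mean count: 40 × 0.25 × d = 10d.
- Variances: 40² × 0.25² + 40 = 140 in one group, and 100 + (40 − 10d) in the other.
- AUC = Φ(difference / √sum of variances).
- d = 0.3: Φ(3 / √277) = 0.57.
- d = 0.5: Φ(5 / √275) = 0.62.
- d = 0.8: Φ(8 / √272) = 0.69.

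**Step 5: after normalisation.** The slopes on area fall to between −0.08 and 0.00, and no correlation with ROI area across the simulated patients exceeds 0.08 in absolute value. Blob density and RLN / N keep their link with texture scale (about −0.93 to −0.96). GLN / N shows almost none (0.04 to 0.14). That is expected here, because the simulation varied spatial scale while holding the gray-level distribution fixed.

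**The case against.** **The premise may not apply.** Choosing an ROI by hand need not mean tracing the muscle. A box of standard size placed by hand fits the same words, and with equal areas the problem disappears. The full protocol may fix the size, and software may output normalised values. This stands, and it makes the point conditional. It does not dispose of it: the article specifies a count per ROI and names the non-uniformity parameters without normalisation, in a section detailed enough to give the pixel distance and angles for the co-occurrence matrices.

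**The stronger reading fails.** A reader might infer that these three parameters are raw totals that measure size instead of muscle quality. That is not supported. GLN and RLN are already divided once by the number of runs, although they still grow with area. Blob count and RLN kept clear texture information at every area CV tried, and at 10% and 20% they followed texture more closely than area. Only GLN became mainly a size measure, from a CV of about 20%.

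**The magnitudes are assumed.** This stands. The area CV, the 40 blobs and the group differences have no source in the article. The simulated blob rule (a threshold) is also not the article's rule of neighbouring areas with similar echo-intensity. The proportionality should hold for any rule that detects blobs locally; the exact figures need not.

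**The duplication of size is not shown directly.** The model's size measures concern the rectus femoris, while the sagittal images described under Muscle architecture processing and analysis are of the vastus lateralis. This stands against any claim that the parameters simply repeat rectus femoris area.

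**Existing safeguards.** The ICCs above 0.90 cover thickness and cross-sectional area, not ROI drawing or texture. The BMI adjustment in the limitations section is aimed at subcutaneous fat. The variance inflation step acts only on variables entered in the model. None of them removes the confounding. Histogram moments such as mean, SD, skewness and kurtosis are not totals, so that part of the second aim is not affected.

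**Conclusion.** The point holds in a conditional form. As specified in the article, blob count per ROI, gray level non-uniformity and run length non-uniformity mix texture with ROI area. Unless ROI size is fixed or the parameters are normalised, their correlations with function or with morbidity and mortality factors could partly reflect size.

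The near-proportional scaling is firm under the standard definitions (slopes 0.92 to 0.995). The practical effect is not known, because it depends on how much ROI area varies between patients. The AUC range of 0.57 to 0.69 is illustrative and rests on the assumptions shown.

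The point is limited to three of the many listed image parameters, to the image-analysis aim and to the planned correlations. A reader might extend it to the main analysis. The article does not support that, because none of the three parameters is among the eight predictors, and the sample size of 500 does not rest on them.

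**What to change.** - Analyse blobs per mm² of ROI in place of the count per ROI.
- Divide gray level and run length non-uniformity once more by the number of runs.
- Alternatively, compute the texture and blob parameters in an ROI of fixed size in mm placed inside the muscle. If this is already the practice, one sentence saying so settles the point.
- In either case, report ROI area alongside these parameters so that a reader can see whether it differs between the groups compared.

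The cost is a division in the image-analysis script and a sentence in the protocol. No new data are needed, since the areas and run counts come from the same images. A fixed ROI would use somewhat less of large muscles.

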### Muscle architecture processing and analysis

Muscle thickness, pennation angle, and muscle fiber length will be assessed using ultrasound technology employing the SonoSite Edge II Ultrasound system (M Turbo Ultrasound system, SonoSite, Bothell, WA, USA), as described above [37]. Participants will be positioned in a seated posture with hip and knee angles set at 90°, ensuring that limb muscles are relaxed to prevent compression or deformation due to seating. To standardize measurements, the length of the femur (from the greater trochanter to the medial condyle) will be measured, and a mark will be placed at the lower third using a hypoallergenic pen for optimal probe placement.

A 15–6 MHz transducer probe (HFL 50×, SonoSite, USA), coated with water-soluble transmission gel (AquaSonic^©^) to enhance acoustic contact without causing pressure on the dermal surface, will be positioned perpendicular to the dermal surface of the vastus lateralis (VL) muscle, aligned with the muscle's median longitudinal plane. Three sagittal plane sonographs of the VL will be digitized, and the images will be transferred to a computer for analysis using ImageJ Software^©^ (National Institute of Health, Bethesda, MD, USA). To ensure consistency across the six participating centers, all ultrasound evaluations will be conducted using the same ultrasound system (SonoSite Edge II, SonoSite Inc., USA) equipped with the HFL 50× linear array transducer (15–6 MHz). Prior to data collection, all evaluators underwent a centralized training program, which included theoretical and practical sessions to ensure methodological homogeneity. Additionally, a pilot study was conducted to evaluate intra- and inter-rater reliability, with repeated measures analyzed using intra-class correlation coefficients (ICC). Excellent reproducibility was observed, with ICC values exceeding 0.90 for both muscle thickness and cross-sectional area.

All sonographic images will be obtained in a standardized position: participants seated with 90° hip and knee flexion, and the probe placed perpendicularly at the distal third of the thigh, as marked based on femur length. Water-based transmission gel will be used to avoid pressure artifacts. The acquisition protocol includes three sagittal plane images of the vastus lateralis, and a fourth M-mode image to assess contraction potential and relaxation velocity. All ultrasound operators were blinded to the frailty classification of the participants during image acquisition. The reproducibility of ultrasound measurements was confirmed during a pilot study prior to data collection, with intra- and inter-rater intraclass correlation coefficients (ICC) exceeding 0.90 for both muscle thickness and cross-sectional area, indicating excellent agreement.

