### Materials

Measurement variables evaluated in patients include:

Manual grip strength: The peak grip force was measured using a hydraulic hand dynamometer (JAMAR, Sammons Preston Rolyan, Sammons Court Bolingbrook, IL, USA) across a range of 0 to 90 kg. This device has been validated, shown to be reproducible, and deemed reliable for assessing grip strength in older individuals [22].Quality of life: measured with the EuroQol-5D, where mobility, personal care, daily activities, pain/discomfort, anxiety, or depression are assessed [23].Barthel Index: Assesses the level of independence of the subject with respect to the performance of activities of daily living [24].Trunk control test: Designed for the assessment of the patient's motor impairment [25].Intensity of Pain: Using the NPRS [26].Ultrasound image: The cross-sectional area and thickness of the rectus femoris muscle will be measured. In addition, contraction potential, contraction-relaxation velocity data will be taken by M-Mode ultrasound [27].The State-Trait Anxiety Inventory (STAI): Assessing state and trait anxiety [28].Kinesiophobia (TSK): Using the Tampa Kinesiophobia Scale, measuring fear of movement [29].Beck Depression Inventory (BDI): It measures depressive symptoms and the severity of depression [30].

Figure 1 illustrates the collection of variables in the older adult population of the study. Figure 2 summarizes the study workflow, from participant recruitment and assessments to the machine learning pipeline for prediction and analysis.

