**Assessments**		
Manual grip strength	X	X
EQ-5D-5L	X	X
Barthel index	X	X
Trunk control test	X	X
BDI	X	X
VAS	X	X
GLIM	X	X
MRCSS	X	X
STAI	X	X
TSK	X	X
TUG	X	X
Adverse events		X

Timeline of procedures including enrollment, assessments, and ultrasound imaging. Abbreviations: EQ-5D-5L: EuroQol 5-dimensions 5-levels; BDI: Beck Depression Inventory; VAS: visual analogue scale; GLIM: Global Leadership Initiative on Malnutrition; MRCSS: Medical Research Council Sum Score; STAI: State-trait Anxiety Inventory; TSK: Tampa Scale of Kinesiophobia; TUG: Timed Up and Go test.

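### The only ultrasound acquisition described (sagittal vastus lateralis images plus one M-mode image) cannot yield the primary model's two ultrasound predictors, rectus femoris cross-sectional area and thickness

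*Protocol article*

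**What the plan says.** The Materials section of the protocol article defines the B-mode measurements: "The cross-sectional area and thickness of the rectus femoris muscle will be measured". It adds that "contraction potential, contraction-relaxation velocity data will be taken by M-Mode ultrasound", without naming the muscle.

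The Statistical analysis section builds the model for the dichotomised Barthel index from "manual grip strength, EuroQoL-5D, NPRS, cross sectional area and thickness of the rectus femoris, STAI, TSK and BDI as explanatory variable". The Sample size calculation section repeats this list and calls it the study's main analysis.

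The section on muscle architecture processing and analysis is the only place that says how images are taken. It opens with thickness, pennation angle and fibre length as outputs, and places the probe over the vastus lateralis along the muscle's longitudinal plane at the lower third of the femur. It then says "Three sagittal plane sonographs of the VL will be digitized". Its last paragraph sets one seated position and one probe site for all sonographic images and continues: "The acquisition protocol includes three sagittal plane images of the vastus lateralis, and a fourth M-mode image", the last of these for contraction potential and relaxation velocity. The same section twice reports pilot ICCs above 0.90 for thickness and cross-sectional area, without stating a muscle or plane.

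**The concern.** The model and the imaging procedure describe different measurements. An operator who follows the procedure finishes with three longitudinal vastus lateralis images and one M-mode image. Rectus femoris area and thickness cannot be read from those.

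The study's first stated aim is to relate ultrasound muscle variables to the geriatric assessment. The Discussion presents cross-sectional area as an advance over earlier studies that mostly measured thickness alone. If the ultrasound terms in the main model are missing, or are filled with values from another muscle under the same variable name, the model cannot support a statement about rectus femoris. The Implications and limitations section also relies on reliability testing to offset operator dependence. That reassurance is incomplete while the muscle and plane behind the ICCs are unknown.

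**Working it through.** **1. Predictors that the sample size counts.** From the Statistical analysis and Sample size calculation sections: grip strength, EuroQoL-5D, NPRS, rectus femoris cross-sectional area, rectus femoris thickness, STAI, TSK and BDI, so k = 8. The stated rule is n = 100 + 50 × k. With k = 8, n = 100 + 400 = 500, which reproduces the plan's figure. The two rectus femoris variables are therefore counted separately, and they are the only ultrasound terms: 2 of 8.

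**2. What the described images can supply.**

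| Quantity | Muscle and view needed | In the described set? |
|---|---|---|
| Rectus femoris thickness (model) | Rectus femoris, B-mode | No: the B-mode images are of vastus lateralis |
| Rectus femoris cross-sectional area (model) | Rectus femoris, transverse | No: different muscle and different plane |
| Cross-sectional area (pilot ICC) | A transverse view of some muscle | No: the B-mode images are sagittal |
| Vastus lateralis thickness, pennation angle, fibre length | Vastus lateralis, longitudinal | Yes, but not in the model |
| Contraction potential, relaxation velocity | M-mode, muscle not stated | Yes, but not in the model |

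The two model terms fail on muscle, and the area fails on plane as well. The unnamed M-mode muscle does not rescue the area, because an M-mode trace gives no cross-sectional area whichever muscle it comes from.

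**3. Effect on the predictor count.** N = 500 is not in error for the model as stated. For illustration, the same rule gives:
- area dropped, one thickness term kept: k = 7, n = 100 + 350 = 450;
- both terms dropped: k = 6, n = 100 + 300 = 400;
- both replaced by vastus lateralis thickness, pennation angle and fibre length: k = 6 + 3 = 9, n = 100 + 450 = 550, above the planned 500.

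The count should therefore be restated if the predictors change.

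**The case against.** The strongest reply is that this is incomplete reporting. Several parts of it stand.

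- Materials states plainly that the rectus femoris variables will be measured. A reader might infer that they are never obtained; the documents do not support that. What they show is that the described procedure does not produce them.
- The verb introducing the image list is not strictly exhaustive, and the phrase covering all sonographic images governs position and probe site, not the list. Two measurement sets, one of them undescribed, is a possible reading. Against it, the count to a fourth image reads as a closed set.
- A pilot ICC for cross-sectional area suggests that some transverse scan was made. That weakens any claim that the data will be missing, but it leaves open which muscle was scanned.
- A reader might infer that the six centres will scan different muscles. The article reports centralised training, one ultrasound system and transducer, and a common evaluation by all investigators beforehand, so this is not a strong argument.
- A reader might conclude that the study could not examine ultrasound at all. Texture, architecture and M-mode variables remain available for the planned correlation analyses; the problem is confined to the main model.
- The pain scale is a separate matter. Materials has "Intensity of Pain: Using the NPRS", as does the model, while the Table 1 legend lists "VAS: visual analogue scale". This is a minor table inconsistency. It does not show that NPRS will go uncollected, so counting 3 of 8 predictors as affected is not justified.

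Condensation in an article does not answer the point. It explains missing detail, whereas this article gives position, site, probe, plane, muscle and image count in full, for a muscle that the model does not use.

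**Conclusion.** The concern holds as a contradiction within the protocol article. The only acquisition described cannot yield the primary model's two ultrasound predictors (2 of 8, and all of its ultrasound content), nor the cross-sectional area for which reliability is claimed. It should be resolved before the model is fitted, because it determines what the model can say about ultrasound.

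The conclusion rests on reading the listed images as the full set, which the text favours but does not prove. If an undescribed transverse rectus femoris scan exists, the data may be sound and the text still needs correcting. If it does not, the two predictors cannot be analysed as specified. The documents do not settle which of these applies.

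**What to change.** Reconcile Materials, the Statistical analysis and Sample size calculation sections with the acquisition section:

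1. For each ultrasound predictor, state the muscle, plane, probe site and number of images. If the rectus femoris predictors are kept, describe a transverse rectus femoris acquisition, with its own site and number of images. The existing mark is described for vastus lateralis and should not be assumed to serve.
2. Name the muscle used for the M-mode image.
3. State the muscle and plane to which the pilot ICCs refer.
4. If only vastus lateralis was scanned, redefine the two predictors as the vastus lateralis measures actually obtained, remove cross-sectional area from the model and from the claims made for the study, and restate the predictor count against N = 500.
5. Separately, list the same pain scale in Table 1 as in Materials and the model.

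**Cost.** If a rectus femoris scan already exists, the cost is wording only. If it does not, participants not yet scanned need a brief extra still acquisition with the same probe. The Study design section gives April 2024 to June 2025, so some participants may already have been scanned. For them the predictors must follow what was acquired, because a missing view cannot be added without recalling them. Redefining the predictors changes the primary model, so it should be documented as a change before analysis.
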